### Economic analysis

The economic analyses are undertaken from a societal perspective, taking into account intervention costs, direct medical costs, direct non-medical costs and indirect costs during the study period
[38]. Indirect costs refer to lost resources and opportunities resulting from the disease. We will assess health service uptake and production losses at T0, T1, T2 and T3 based on the TIC-P. Full economic costs due to care utilisation and production losses are obtained from the national manual for cost prices in the health care sector. The intervention costs concern the costs related to the internet application, the advertisement and the training/salary of the coaches. Indirect costs include production losses both in paid labour and in the domestic sphere. In addition, both costs due to work loss and work cut-back are assessed, as work cut-back in patients with affective symptoms may be substantial. To calculate indirect costs the friction cost method is used, thereby taking the replacement of sick employees into account, resulting in more conservative cost estimates than the human capital approach. As the timeframe used in the present study is relatively short, costs are not discounted nor corrected for inflation.

To account for the possible non-normality of the cost data, sample errors and 95% confidence intervals are based on resampling methods (bootstrapping) using 2,500 replications.

A cost-effectiveness analysis assesses the costs per recovered patient
[39]. Quality of life is assessed at each assessment point with the Euroqol, and the average quality of life during the study period is calculated.

A cost-utility analysis is similar to a cost effective study, but assesses the incremental costs per QALY gained during the study period (instead of the incremental costs per recovery).

We will report the incremental cost-effectiveness ratio. The Incremental cost-effectiveness ratio (ICER) is the ratio between the difference in costs (between experimental and control condition) and the difference in effects (between experimental and control condition), where costs is the average annual per capita cost and effects is the percentage of participants that recovered from their depression.

We will report the ICER, the scatter of the bootstrapped ICERs on the ICER plane and the ICER acceptability curve for the probability that the intervention dominates care as usual for a series of willingness-to-pay ceilings. Use will be made of the pertinent guidelines for health economic evaluation.

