**Flowchart selection, inclusion, intervention and measurement.**

### Inclusion and exclusion criteria

We will include participants who are at risk for developing postpartum depression. More specifically, we will include participants of 18 years and older, who are pregnant but are at least 10 weeks before the expected delivery date, and have at least mild symptoms of depression or anxiety. Symptoms of depression are measured with the Center for Epidemiological Studies Depression scale (CES-D) and symptoms of anxiety with the Hospital Anxiety and Depression Scale- Anxiety subscale (HADS-A)
[20, 21]. Patients are eligible if they score at least 16 on the CESD and/or 8 on the HADS-A. Participants who indicate that they either intend to harm themselves or want to attempt suicide (as assessed by one question of the Web Screening Questionnaire (WSQ)
[22]) will be excluded. They are advised to consult their general practitioner to obtain more tailored care. Receiving psychiatric treatment including psychotherapy or the use of psychopharmacological agents such as antidepressants is allowed. Any additional treatments will be monitored through patients self-report at the end of study.

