### Assessments

All assessments are based on self-report and will take place online (Table 
1). We will measure at baseline (T0), 10 weeks later (although it is possible to finish the intervention in 6 weeks we know that there will be some people who need more time. To ensure that the post-test assessment takes place after completing the intervention we will perform the post-test assessments after 10 weeks.), when the intervention group has finished the intervention (T1), 4 weeks before the expected day of birth (in order to registrate symptoms of relapse (T2), and 6 weeks after delivery (T3). Participants starting the intervention after 24 weeks of pregnancy will not be assessed at T2, since the time period between T1 and T2 will be too small.

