### Sample size and statistical analysis

Analyses will be conducted according to intention-to-treat as well as per protocol principle. To study differences between the conditions we will use linear mixed models with symptoms of depression and anxiety as dependent variables, time indicators and treatment dummy as predictors, since these types of models account for drop out over time. We will compute both within group effect sizes and between group effect sizes. The within group effect sizes are standardized differences of (predicted) means of the follow up scores and baseline scores. The between group effect sizes concern differences between within group effect sizes. We assume that the between group effect size (Cohen’s d) at the end of the study will be at least 0.40, because this has been demonstrated in a meta-analysis on supported internet treatments in general
[13] and in previous studies using the same problem solving internet treatment
[19, 25]. Using an alpha of 0.05 (two-tailed), a statistical power (1-bèta) of 0.80, and an attrition rate of 30%
[19] we need 143 respondents in each arm. All analyses will be conducted using SPSS for Windows, version 20 and STATA 10.0.

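### Short follow-up justifies not discounting costs, but it does not justify ruling out inflation correction, which may leave manual prices and intervention costs in different price years

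*Protocol article*

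**What the plan says.** All of the cost rules are in the protocol article, under Economic analysis.

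- Discounting and inflation: "As the timeframe used in the present study is relatively short, costs are not discounted nor corrected for inflation". No other reason is given for either decision.
- Valuation of care and lost production: "Full economic costs due to care utilisation and production losses are obtained from the national manual for cost prices in the health care sector". The edition and reference year of the manual are not given.
- Intervention costs: "The intervention costs concern the costs related to the internet application, the advertisement and the training/salary of the coaches". The article does not say whether these are actual outlays or tariffs, or in which price year they are expressed.
- Use of the costs: the ICER "is the ratio between the difference in costs (between experimental and control condition) and the difference in effects (between experimental and control condition"). It is reported per recovered patient and, in the cost-utility analysis, per QALY.
- The section closes with a general commitment: "Use will be made of the pertinent guidelines for health economic evaluation".

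**The concern.** Discounting and price indexation answer different questions. Discounting concerns when, within a woman's follow-up, a cost falls, so a short follow-up is a good reason to omit it. Indexation concerns whether the unit prices used are in the money of the same year. That depends on the reference year of each price source. A 16-week follow-up can still be valued with prices that are several years old.

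The plan has at least two kinds of cost: manual unit prices, and an intervention budget that includes items such as application and advertising costs. Read literally, the inflation rule rules out bringing the two to one basis.

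A mismatch would not cancel between arms. Under Study design and Control group, controls are offered the programme only after the last follow-up, so within the trial the intervention cost falls on the experimental arm alone. The manual-priced costs enter as a difference between arms. Any misalignment therefore carries into the incremental cost, both ICERs, the ICER plane and the acceptability curve.

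**Working it through.** The plan states no price year, inflation rate, unit cost or expected cost difference, so there is no figure of its own to reproduce on this point. The check has three steps.

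**1. Does short follow-up support each half of the rule?**

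The inclusion criteria admit women "who are pregnant but are at least 10 weeks before the expected delivery date", and the last assessment is "6 weeks after delivery (T3").

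- Latest entry, delivery on the due date: 10 + 6 = 16 weeks, or 16/52 = 0.31 years.
- Upper bound, taking a 40-week pregnancy (an assumption) and entry at its very start: 40 + 6 = 46 weeks, or 46/52 = 0.88 years.

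Follow-up is under one year, which supports not discounting. Neither figure says anything about the price years of the manual or of the intervention costs.

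**2. How large could the index factor be?**

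Assume that the manual prices are g years older than the intervention prices and that inflation is r a year. Then f = (1 + r)^g.

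| g (years) | r = 1% | r = 2% | r = 3% |
|---|---|---|---|
| 0 | 1.000 | 1.000 | 1.000 |
| 1 | 1.010 | 1.020 | 1.030 |
| 2 | 1.020 | 1.040 | 1.061 |
| 3 | 1.030 | 1.061 | 1.093 |
| 4 | 1.041 | 1.082 | 1.126 |
| 5 | 1.051 | 1.104 | 1.159 |

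The assumed range is 1.00 to 1.16.

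**3. What does that do to the incremental cost?**

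Set the intervention cost to 1. Let S be the between-arm saving in manual prices, negative if care and production costs rise.

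- Net cost as written: 1 − S
- Net cost after indexing: 1 − S·f
- Relative change: −S(f − 1)/(1 − S)

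For a fixed effect difference, the ICER changes by the same percentage. At the top of the range, f = 1.159:

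| S (illustrative) | As written | Indexed | Change |
|---|---|---|---|
| 0.25 | 0.750 | 0.710 | −5.3% |
| 0.50 | 0.500 | 0.420 | −15.9% |
| 0.90 | 0.100 | −0.043 | −143% |
| −0.50 | 1.500 | 1.579 | +5.3% |

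With g = 0, every change is zero. For S = 0.90 the sign flips only when f exceeds 1/0.90 = 1.11. In the first table that happens only at 3% inflation with a lag of 4 or 5 years (1.126 and 1.159). The absolute shift is S(f − 1), at most about 16% of the manual-priced difference. It looks large in relative terms only when the two components nearly cancel.

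**The case against.** A reader might infer that savings and intervention costs are in different price years, and that the ICER is therefore skewed against the intervention. The documents do not support this. They give no manual edition, no reference year and no valuation method for the intervention costs, and they predict no savings. The programme was adapted from an existing one (Intervention section), so some application costs could even predate the trial. If the price years match, there is no bias. If care costs rise, or if the manual is the newer source, the direction reverses. This part of the objection stands in full.

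The sentence can also be read as meaning only price change within the study period, which would not prevent the choice of one base year. That is a fair reading, but the wording carries no such limit, and the analyst has to apply what is written. The general commitment to guidelines does not settle the matter: it names no price year and does not override a specific rule in the same section.

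A condensed article may leave the price year to a fuller document, and that omission is not the point here. The point is a stated exclusion resting on a reason that does not support it.

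Finally, the planned bootstrap would show a near-zero cost difference straddling the quadrants, so a change of sign in the point estimate should not be over-read. That is true. However, resampling women with the same unit prices reflects sampling error only, and every replicate would carry the same misalignment.

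**Conclusion.** The point holds conditionally. Short follow-up supports the decision not to discount and gives no support to the decision not to correct for inflation. If the manual and the intervention costs have different price years, the rule as written leaves them unaligned, and the incremental cost and both ICERs may be biased.

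Neither size nor direction can be fixed from the document. Under the assumed lag of 0 to 5 years at 1% to 3% a year, the manual-priced component would need a factor of 1.00 to 1.16. The effect on net cost runs from none, through about 5% or 16% when savings are a quarter or half of the intervention cost, to a possible change of sign when they nearly cancel. The lag, the inflation rates and the savings are all illustrative.

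The consequence is confined to the economic evaluation, a secondary outcome. The symptom and perinatal analyses are untouched.

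**What to change.** Keep the no-discounting rule with its reason, delete the exclusion of inflation correction, and state a common price basis. Suggested text: *Costs are not discounted because follow-up is under one year. All unit prices and intervention costs are expressed in one stated price year, using a published price index.*

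The cost is one sentence and one index factor per price source, settled before the economic analysis is run. No data collection changes. If the sources turn out to share a price year, the factor is 1 and the results do not change.

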### Quality of life

Quality of life is assessed with the Euroqol
[34–37]. This is self report questionnaire which measures quality of life and consists of 5 health state dimensions (pain/discomfort, depression/anxiety, mobility, self-care and usual activity) giving an indication of the own health state. The value that the individual or the society may place on a particular health state is expressed in a utility score. This utility score varies by a number between 0 (worst imaginable condition: death) and 1 (perfect health). In the Netherlands the tariff of valuation to determine the utility score is used to calculate quality-adjusted life years (QALYs) by multiplying the utility score with the amount of years the health state exists.

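### The economic analysis makes no stated use of the T0 utility and T0 cost and does not tie its average quality of life to the QALY: a free gain in precision, not an error

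*Protocol article*

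**What the plan says.** All of the following is in the protocol article.

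- **Utility summary (Economic analysis):** "Quality of life is assessed at each assessment point with the Euroqol, and the average quality of life during the study period is calculated". Table 1 lists the Euroqol at T0, T1, T2 and T3, so the assessment points include the one before randomisation.
- **QALY (Quality of life):** obtained by "multiplying the utility score with the amount of years the health state exists". The Economic analysis section says that the cost-utility analysis uses QALYs, but not how the averaged utility relates to them.
- **Costs (Economic analysis):** "We will assess health service uptake and production losses at T0, T1, T2 and T3 based on the TIC-P". The role of the T0 cost is not stated.
- **Estimator (Economic analysis):** the ICER is the between-arm difference in costs over the between-arm difference in effects. The effect named there is the percentage recovered from depression; the cost-utility analysis replaces recovery by QALYs. Intervals come from 2,500 bootstrap replications.
- **Visit pattern (Assessments):** "Participants starting the intervention after 24 weeks of pregnancy will not be assessed at T2", so some women have four Euroqol values and others three.

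No covariate is named for the economic comparison. None is excluded either, and the section closes by referring to health-economic guidelines.

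**The concern.** The economic section states its own estimator in some detail: friction costs, no discounting, the number of bootstrap replications and the ratio itself. Within that detail, the baseline value of neither utility nor cost has a role. The symptom analysis in the same article does use baseline, since its between-group effect sizes are differences in change from T0.

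Two things are at stake. The first is precision. A woman's T0 utility predicts her later utility, and a summary that contains T0 is correlated with it by construction. Leaving this out makes the interval for the QALY difference wider than the data require, and any chance T0 difference between arms is carried into the estimate.

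The second is definition. Visits are unequally spaced and some women skip T2. A simple mean of visits and a time-weighted QALY therefore weight T0 differently, and the text does not say which average is meant.

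**Working it through.** **Number of completers.** For d = 0.40, two-sided alpha 0.05 and power 0.80, the normal formula gives 2(1.960 + 0.842)²/0.40² = 98.1, so 99 per arm. The t-test version gives 100 (99.08 rounded up). With 30% attrition, 100/0.70 = 142.9, so 143 per arm, which reproduces the article's figure. I use 100 completers per arm below.

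**Assumptions.** The article gives no SD or correlation for utility or cost. I assume equal variance at each visit, a common between-visit correlation rho of 0.3, 0.5 or 0.7, and a utility SD of 0.15 to 0.25. Delivery is taken at 40 weeks, so T2 falls at week 36 and T3 at week 46; T1 is 10 weeks after entry.

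**Formulas.** Let the summary have visit weights w that sum to 1, with w0 on T0.
- Share of a T0 difference carried into the summary: b = rho + (1 − rho)w0.
- Variance of the summary, in units of SD²: V = rho + (1 − rho)Σw².
- Share of variance removed by adjusting for T0: R² = b²/V.
- SE after adjustment divided by SE before: √(1 − R²).

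**Example 1, simple four-visit mean.** Here b, V and R² all equal (1 + 3rho)/4 = 0.475, 0.625, 0.775. The SE factor is √0.525 = 0.725, √0.375 = 0.612, √0.225 = 0.474.

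**Example 2, time-weighted, entry at 12 weeks.** Visits at weeks 12, 22, 36 and 46 give trapezium weights 5, 12, 12, 5 over 34, so w0 = 0.147 and Σw² = 338/1156 = 0.292. At rho 0.5, b = 0.574, V = 0.646, R² = 0.509 and the factor is 0.701.

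| Utility summary | Weight of T0 | SE factor, rho 0.3 | rho 0.5 | rho 0.7 |
|---|---|---|---|---|
| Simple mean, four visits | 0.250 | 0.725 | 0.612 | 0.474 |
| Simple mean, three visits (no T2) | 0.333 | 0.683 | 0.577 | 0.447 |
| Time-weighted, entry week 12 | 0.147 | 0.824 | 0.701 | 0.545 |
| Time-weighted, entry week 20 | 0.192 | 0.781 | 0.661 | 0.513 |
| Time-weighted, entry week 28 (no T2) | 0.278 | 0.752 | 0.638 | 0.495 |

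**Size of a chance imbalance.** With 100 per arm, the SE of a T0 difference is √(2/100) = 0.141 SD, and a difference beyond 0.2 SD in either direction has probability of about 16%. With utility SD 0.20, one SE is 0.20 × 0.141 = 0.028. The four-visit mean carries 0.475, 0.625 or 0.775 of it, which is 0.013, 0.018 or 0.022 on the mean-utility scale. For a QALY over 26 weeks (entry at week 20), b is 0.435, 0.596 or 0.758. Multiplying by 0.0283 × 26/52 gives 0.006, 0.008 or 0.011 QALY. Over SD 0.15 to 0.25 the range is 0.005 to 0.013 QALY.

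**Costs.** If r is the correlation of T0 cost with follow-up cost, the SE factor is √(1 − r²): 0.995, 0.954, 0.866 and 0.714 at r = 0.1, 0.3, 0.5 and 0.7.

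**The case against.** The strongest reply is that this is a condensed article. It never calls the comparison unadjusted, a regression-adjusted increment is also a difference between arms, and covariates are commonly left to the full protocol or a health-economic plan. That stands: the absence of a named covariate is not a fault in itself.

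A reader might also infer more than the text supports:

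- **That the result will be biased.** With 1:1 randomisation the unadjusted difference is unbiased on average, and the bootstrap interval already reflects chance imbalance.
- **That T0 should not be in the average.** An area-under-the-curve QALY starts at T0 and needs that value. The issue is only whether the comparison is adjusted for it.
- **That the average is an unweighted mean of visits.** An average over a period can equally be time-weighted, and multiplied by duration it then equals the QALY under Quality of life. The T0 weights of 1/4 and 1/3 apply only on the unweighted reading.
- **That T0 utility can overturn the reported ICER.** The ICER spelled out has recovery as its effect, which T0 utility does not enter. Only the cost-utility ratio is exposed to it. A T0 cost imbalance can reach the cost difference, which both ratios share.
- **That the imbalance rivals the treatment effect.** The article gives no expected QALY effect, so no such comparison can be made.
- **That T0 costs are added to the follow-up total.** The article only says that they are collected.

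What survives is narrower. The stated estimator makes no use of baseline data already in hand, and two sections describe the utility summary without linking them.

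**Conclusion.** This is a free improvement of minor to moderate weight, not a demonstrated error. The unadjusted analysis would be valid but less precise than it could be. For the cost-utility analysis the gain is useful across the assumed range: the SE falls to 0.72–0.47 of its value for a four-visit mean, and to 0.82–0.55 for a time-weighted QALY with entry at 12 weeks. For costs it runs from negligible (0.5% of the SE at r = 0.1) to 29% (at r = 0.7), and the article gives no basis for choosing within that range.

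All these factors rest on assumed correlations, and the imbalance figures also on an assumed utility SD. The time-weighted factors each hold for one entry week. Follow-up runs from 34 weeks (entry at 12) to 18 weeks (entry at 28), so QALY totals pooled over entry weeks also vary with duration, which T0 utility does not explain. The sample size is unaffected.

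**What to change.** In the Economic analysis section, or in the full health-economic plan if it is silent on this, state:

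1. The QALY is the time-weighted area under each woman's utility curve from T0 to T3, in line with the Quality of life section. Say whether the average quality of life is this area divided by follow-up time. For women without T2, the curve runs straight from T1 to T3.
2. The incremental QALY is the arm coefficient from a regression of QALY on arm and T0 Euroqol utility.
3. The incremental cost is the arm coefficient from a regression of post-randomisation cost on arm and T0 TiC-P cost. T0 cost serves as a covariate and is not part of the follow-up total.
4. Both regressions are refitted in each of the 2,500 bootstrap replicates, on the same resampled women, so that the cost and QALY increments stay paired.

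The cost is a few sentences and a few lines of code. The T0 Euroqol and TiC-P are already scheduled, and neither the sample size nor the visit plan changes.

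### The ICER is defined with an annual cost, although costs are otherwise counted over the study period and no woman is followed for a year

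*Protocol article*

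**What the plan says.** All of the following is in the Economic analysis section of the protocol article unless another section is named.

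- The opening sentence sets the cost horizon. Among the items counted are "direct non-medical costs and indirect costs during the study period".
- Resource use is measured only at the trial visits: "We will assess health service uptake and production losses at T0, T1, T2 and T3 based on the TIC-P".
- The short horizon is the reason given for not discounting: "As the timeframe used in the present study is relatively short, costs are not discounted nor corrected for inflation".
- The cost-utility analysis "assesses the incremental costs per QALY gained during the study period".
- The ICER is then defined as the difference in costs over the difference in effects, "where costs is the average annual per capita cost and effects is the percentage of participants that recovered from their depression".
- The acceptability curve is to show "the probability that the intervention dominates care as usual for a series of willingness-to-pay ceilings".

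Inclusion and exclusion criteria sets the latest entry at ten weeks ahead of the due date and gives no earliest gestational age. Assessments places T3 at six weeks postpartum.

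**The concern.** Two cost horizons stand in one section. The opening and the cost-utility sentence use the study period; the ICER definition uses a year. Nothing in the article reconciles them or says how costs seen over part of a year become annual.

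The discrepancy does not cancel between arms. If costs in both arms are multiplied by a factor, so is their difference. The difference in recovery is a difference in percentages within the trial and is not multiplied by anything. Some cost items also have no annual rate: the course has six lessons with coach feedback, and each woman has one delivery within follow-up.

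Cost-effectiveness is the third aim listed in the Background. An analyst who follows the ICER sentence and one who follows the opening sentence would report different costs per recovered patient from the same data.

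**Working it through.** The article states no ICER, annual cost or length of follow-up in weeks, so there is no planned figure to reproduce. The check is how far an annual cost lies from what is observed.

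**Inputs**
- Latest entry: 10 weeks before the due date (Inclusion and exclusion criteria).
- Last assessment: 6 weeks after delivery (Assessments).
- Assumed: delivery at 40 weeks, and a year of 52 weeks.
- Assumed: any entry week *g* earlier than 30. The article gives no earliest entry.

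**Length of follow-up and scaling factor**

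Follow-up in weeks = (40 − *g*) + 6. Annualisation factor *k* = 52 / follow-up.

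| Entry week *g* | Follow-up (weeks) | *k* |
|---|---|---|
| 30 (latest allowed) | 10 + 6 = 16 | 52/16 = 3.25 |
| 24 | 16 + 6 = 22 | 52/22 = 2.36 |
| 10 (assumed) | 30 + 6 = 36 | 52/36 = 1.44 |
| 4 (assumed) | 36 + 6 = 42 | 52/42 = 1.24 |

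Even a count from gestational week 0 gives 40 + 6 = 46 weeks, so no woman delivering at term is observed for a year. Only the 16-week figure follows from the stated criteria, and it too supposes delivery on the due date.

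**Effect on the ICER under uniform scaling**

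Write ΔC for the study-period cost difference and ΔE for the recovery difference. Scaling every cost by the same *k* gives *k*·ΔC / ΔE, which is *k* times the study-period ICER.

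**Does the direction hold under other methods?**

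The values here are assumed for illustration only: ΔE = 0.15, one-off intervention cost 300, other cost difference −100.

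- Study period: (300 − 100)/0.15 = 1333.
- All costs scaled: 1333 × 52/36 = 1926 at 36 weeks; 1333 × 3.25 = 4333 at 16 weeks.
- Only the other costs scaled: (300 − 100 × 52/36)/0.15 = 1037 at 36 weeks; (300 − 100 × 3.25)/0.15 = −167 at 16 weeks.

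So the ICER can rise, fall or change sign, depending on which costs are annualised. With an other-cost difference of −400 there is a net saving. The study-period ratio is (300 − 400)/0.15 = −667, and uniform scaling at 16 weeks gives −667 × 3.25 = −2167 (from unrounded values). The saving is exaggerated.

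**Acceptability curve**

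Dominance in its technical sense means lower cost and greater effect. Neither condition involves a willingness-to-pay ceiling, so a probability of dominance cannot vary with the ceiling. The quantity that does vary is the probability that incremental net benefit, ceiling × ΔE − ΔC, exceeds zero.

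**The case against.** The strongest reply is that the annual phrase is loose or carried-over wording. The same section refers to the study period for both costs and QALYs and calls the timeframe short, and no annualisation formula is given, so the authors may never have meant to extrapolate. That may be so, but the phrase sits in the sentence that defines the ICER, and no other passage overrides it. The reply bears on how likely the error is, not on whether the text needs correcting.

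Several stronger readings are tempting, and the reply succeeds against them.

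- **That the ICER is inflated, with late entrants weighted most.** This needs a particular method: every cost scaled, and for the weighting a separate factor for each woman. The article gives no method.
- **That the cost per QALY is wrong by the same multiple.** The annual cost is tied explicitly only to the recovery ratio. The cost-utility analysis is called similar, so carry-over is possible, but it is not stated.
- **That QALYs come from an unweighted mean of the visit utilities.** A reader might infer this from the sentence that "the average quality of life during the study period is calculated". It does not say the average is unweighted or that it is the QALY, and the Quality of life section multiplies utility by the time spent in the state.
- **That the acceptability curve would be published as a flat line.** The reference to a series of ceilings makes the standard curve the evident intention. The verb is technically wrong, and that is all.

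It is also fair that costs and quality of life are secondary outcomes, and that the primary outcomes, sample size and data collection are unaffected.

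**Conclusion.** The point stands as an internal inconsistency in the cost horizon. The ICER definition calls for an annual cost, the rest of the section uses the study period, and data exist only from T0 to T3. Followed literally, the definition divides an extrapolated cost by an effect that is not extrapolated.

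Under uniform scaling the magnitude of the ICER would be multiplied by 3.25 for the latest entrants with term delivery, falling to about 1.4 or 1.2 for the two assumed early entry weeks. For the trial as a whole the multiple depends on the mix of entry weeks, which the article does not give. Under other methods the direction is open. The supportable conclusion is therefore a distorted ratio of uncertain direction. The consequence is confined to the economic evaluation. The acceptability-curve wording is a minor, separate correction.

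**What to change.** In the ICER definition, replace the annual per capita cost with the mean total cost per woman from T0 to T3, not annualised, and take the difference between arms. State that the cost-per-recovery and cost-per-QALY ratios both use costs and effects over this same period.

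In the acceptability-curve sentence, replace dominance with the probability that the intervention is cost-effective, meaning incremental net benefit above zero, at each ceiling.

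Both are changes of wording. They need no new data, visits or participants, because the cost questionnaire and the Euroqol are already scheduled from T0 to T3. They should be settled before cost data are seen by arm, so that the choice of horizon cannot depend on the result.
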